## 9.4 Safety analysis

The safety evaluation will include MACCE and AEs, and SAEs related to AMCE exam. The analysis of MACCE will follow similar methodology as the analysis of the

time-to-event outcome (described in Section 9.3.2) based on the safety analysis set (investigational product). The analysis of AEs and SAEs related to AMCE examination will be summarised as for the safety analysis set (patients who received AMCE examination at least once) as a whole.

## **9.5 Exploratory analysis**

The variables planned to be analyzed are provided in the exploratory objectives in section 2.3. Exploratory analyses will examine the predictive value of baseline clinical, demographic, laboratory, procedural characteristics, concomitant medication, and treatment allocation (if possible) as independent predictors of gastrointestinal mucosal injury at baseline, 6 months before randomization, and 12 months. Subsequently, establishing a gastrointestinal mucosal injury scoring system that may identify patients at future risk for clinical gastrointestinal bleeding during long-term antiplatelet therapy.

## **9.6 Subgroup analysis**

The primary and secondary endpoints will be summarised in clinically relevant subgroups of the FAS as a whole and by treatment group. For each subgrouping variable, ORs and two-sided 95% CI will be calculated within each subgroup using a Logistic regression with treatment as fixed effect factors. Formal interaction testing on the ratio scale will be performed using the subgroup  $\times$  treatment allocation as an additional term in the Logistic model.

The following subgrouping variables will be considered:

- Age (<65 years,  $\geq$ 65 years)
- Sex (male, female)
- Diabetes mellitus (yes, no)
- Chronic kidney disease (eGFR<60,  $\geq$ 60 mL/min/1.73m^2)
- Acute coronary syndrome (yes, no)

- Prior history of gastrointestinal bleeding (<24 months, ≥24 month)
- HP infection status (yes, no)
- DAPT duration prior to randomization (>6 months, ≤6 months)

Another subgroup analysis will be performed in patients in whom follow-up was complete vs incomplete or otherwise affected by the COVID-19 pandemic (6-month visit after randomization date: before 2020/1/23, after 2020/1/23).

## **9.7 Investigational medication compliance**

Compliance will be assessed by the investigator and/or study personnel at each visit using pill counts and information. Study drug accountability will be determined by the site monitor while performing routine site visits and at the completion of the study.

Study drug compliance will be assessed using manual pill count at the 12-month in-person follow-up visit. The percentage of study drug compliance for the overall treatment period will be derived for each patient based on pill counts as the number of pills taken (dispensed – returned), relative to the expected number of pills taken. Study drug compliance will be presented descriptively, including mean, median, quartiles and 5% and 95% percentiles.

*Non-compliance is defined as taking less than 80% of dispensed tablets based on manual pill bottle count. The non-compliance patients will exclude from the PP population.*

## **9.8 Sensitivity analyses**

See SAP section 8.

## **9.9 Pre-defined substudy**

The following sub-study is either embedded within the ongoing framework of OPT-PEACE. A general description of planned substudy is provided below.

### **9.9.1 Platelet function**

A subset of patients will participate platelet function substudy. Platelet function testing, including adenosine diphosphate-induced platelet aggregation by light transmission aggregometry and VerifyNow aspirin and P2Y12 testing assessment, will be performed at baseline screening, randomization and at the end of the study in first 102 enrolled patients (34 per group) in the site of PI.

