## 12.2 Methods of statistical analyses

Continuous variables will be summarised as the number of observations, number of missing values, mean, standard deviation, median, quartiles, and range.

Categorical variables will be summarised as the number of observations, number of missing values, frequencies, and percentages.

Baseline clinical, demographic, laboratory and procedural characteristics will be summarized by randomized treatment group.

Demographic and baseline characteristics will be summarized by randomized treatment group and for all randomized subjects combined (i.e., FAS population). Baseline characteristics that will define subgroups of interest for the efficacy and safety analyses are:

- Age group ( $< 65$ ,  $\geq 65$  years)
- Gender (Male, Female)
- Diabetes mellitus (yes, no)
- Chronic kidney disease (yes, no)
- CAD presentation (Stable, Unstable)
- HP infection status at enrollment (positive, negative)
- Antiplatelet treatment status at enrollment ( $>6$  months,  $\leq 6$  month)

**Censoring:** Subjects not experiencing any endpoint will be censored at time of death, last contact date (for subjects who withdraw consent or are lost to follow-up) or 180-day  $\pm$  14 days after randomization, whichever comes first.

**Primary Efficacy Analysis:** The primary endpoint analysis will be conducted according to the intention-to-treat (ITT) principle. The main aim of this study is to determine whether the strategy of 6-month DAPT plus 6-month single antiplatelet therapy is superior to 12-month DAPT in terms of the primary endpoint (gastrointestinal injury) after contemporary DES implantation. The null hypothesis ( $H_0$ ) for this analysis is that the incidence of primary endpoint in the experimental group is same as that of the control group, namely  $P_0=P_1$ . The alternative hypothesis ( $H_1$ ) is that the incidences of primary endpoints in the two groups was not equal, namely  $P_0 \neq P_1$ , and the superiority test is conducted at the 2-sided significance level of 0.05. This analysis will be repeated in the Per-protocol (PP) population to support the main results.

The primary and secondary endpoints will be also analyzed in the following clinically

relevant pre-specified subgroups (Part 12.2). Formal interaction testing will be performed using the subgroup  $\times$  treatment allocation as an additional term in the logistic models.

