- (7) Any active gastrointestinal bleeding or ulcers, or prior gastrointestinal bleeding or ulcers within the last 24 months;
- (8) Prior gastrointestinal tract or abdominal surgery other than simple procedures which would not change the gastrointestinal tract anatomy, such as polyp removal, cholecystectomy or appendectomy;
- (9) Contraindications to the AMCE test, including suspected or known gastrointestinal obstruction, stenosis, fistula, diverticula, etc; presence of gastrointestinal obstruction symptoms such as pain or dysphagia; inoperative conditions or refusal to undergo abdominal surgery if required (ie, if the capsule will not pass and cannot be removed by endoscopy);
- (10) Severe hemorrhoids (phase 3–4 according to guidelines of American Society of Colon and Rectal Surgery);
- (11) LVEF<0.40 on admission by echocardiography;
- (12) Renal dysfunction (eGFR<30 ml/min/1.73m^2);
- (13) Active hepatitis or ALT >3 times upper limits of normal at admission;

- (14) Uncontrolled severe hypertension (>180/110 mmHg);
- (15) Hemoglobin<100 g/L;
- (16) Platelet count<100 × 10^9/L;
- (17) Planned use of a proton pump inhibitor, gastric mucosa protectant or any other antacid agent after study enrollment;
- (18) Required use of oral anticoagulation (warfarin or other factor II or factor X inhibitors);
- (19) Inability to take 12-month DAPT for any reason;
- (20) Mandatory use of >6-month DAPT;
- (21) Any comorbidity with estimated survival time<12 months (eg, progressive cancer, chronic obstructive lung disease, etc);
- (22) Any contraindication to MRI examination, including implantation of an MRI-incompatible pacemaker, defibrillator, or other ferromagnetic material, etc;
- (23) Pregnant or plan to be pregnant within 1 year;
- (24) Any condition that may interfere with any study procedures, such as dementia, immobility, alcohol use, etc;
- (25) Planned surgery within 1 year;
- (26) Taking iron supplement;
- (27) Participating in any other clinical trial of an investigational drug or device that has not met its primary endpoint.

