## **10 Sample size Re-estimation**

Among the first 200 patients enrolled, ~25% had gastrointestinal injury at baseline by screening AMCE (despite clinically absent bleeding or gastrointestinal complaints). Of those who passed the initial exam, only ~65% were eligible for randomization; 17% of patients were noncompliant with the 6-month repeat AMCE exam, and new gastrointestinal ulceration or bleeding was found on the 6-month AMCE examination in 18% of patients. The study sample size was adjusted accordingly so 1000 patients will be screened by AMCE at baseline, with 750 patients enrolled and followed to the 6-month randomization eligibility period to achieve the 480 patients randomized goal.

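### The SAP's prior-bleeding subgroup has a stratum that exclusion 7 empties, and its platelet substudy equates 102 enrolled patients with 34 per group, which needs every one of them to be randomised

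*Supplement*

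**What the plan says.** **Prior bleeding.** SAP sections 7 and 9.6 list eight baseline subgroups, plus a COVID-19 split. One is "Prior history of gastrointestinal bleeding (<24 months" against 24 months or more. Section 9.6 asks for an odds ratio in each stratum and a subgroup-by-treatment interaction term, for the primary and secondary endpoints. Exclusion 7 (SAP 3.2; protocol V1.4, section 4.2) bars active GI bleeding or ulcers and also "prior gastrointestinal bleeding or ulcers within the last 24 months". The protocol's own subgroup list in section 12.2 has no prior-bleeding item.

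**Platelet substudy.** SAP 9.9.1 says that testing "will be performed at baseline screening, randomization and at the end of the study in first 102 enrolled patients (34 per group"), at the lead site. Protocol section 5.3 gives the same 102 and 34. Under SAP 3.2 a patient is enrolled once the screening capsule endoscopy (AMCE) shows no ulceration or bleeding, which is about six months before randomisation. SAP section 10 reports that, of those who passed the initial exam, "only ~65% were eligible for randomization".

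**DAPT duration.** Another SAP subgroup is "DAPT duration prior to randomization (>6 months" against 6 months or less, with no start date given. Protocol section 12.2 has a different variable with the same 6-month cut: "Antiplatelet treatment status at enrollment".

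**The concern.** A prespecified subgroup should have patients in every stratum and a stratum for every patient. The prior-bleeding split fails on both counts. Its interaction test, planned for every primary and secondary endpoint, could not be run, and the analyst would have to invent a recoding after the data are in.

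The substudy figure looks like a simple division of 102 by 3, made at a stage when the patients have no group yet. If a third of them are never randomised, the stated group size describes a substudy that the design does not deliver. A missed baseline sample cannot be taken later.

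The DAPT-duration split raises a milder question: whether a 6-month cut means anything in patients who are all randomised at about 6 months.

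**Working it through.** **1. Prior bleeding: the passages side by side**

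| Patient's history at enrolment | Exclusion 7 | Stratum in SAP 7 and 9.6 |
|---|---|---|
| GI bleed less than 24 months ago | excluded | the recent stratum: 0 expected |
| GI bleed 24 months or more ago | eligible | the remote stratum |
| No GI bleed ever | eligible | none |

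Dating the bleed from randomisation instead does not fill the recent stratum. A bleed already 24 months old at enrolment is older still six months later. For bleeding during the open-label phase, SAP 3.3 names bleeding as an example of an event that makes a patient unsuitable for randomisation, and it takes forward only patients free of clinically overt bleeding. With one populated level, the subgroup-by-treatment term cannot be estimated.

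**2. Platelet substudy**

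Inputs:
- 102 enrolled, 34 per group (SAP 9.9.1).
- Allocation 1:1:1 (SAP 3.3).
- Yield from enrolment to randomisation of about 65% (SAP 10). This agrees with the two losses given there: 1 − 0.17 − 0.18 = 0.65.
- Revised plan 480/750 = 0.64 (SAP 10).
- Loss before randomisation first assumed at 10% (SAP 5).

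The plan's figure is 3 × 34 = 102. It reproduces only at a yield of 100%.

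Formulas: expected randomised = 102 × yield; per group = that ÷ 3; enrolled needed for 34 per group = 102 ÷ yield, rounded up.

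| Basis for yield | Yield | Randomised | Per group | Enrolled needed |
|---|---|---|---|---|
| Implied by the SAP figure | 1.00 | 102 | 34 | 102 |
| 10% loss first planned | 0.90 | 91.8 | 30.6 | 114 |
| Observed, SAP 10 | 0.65 | 66.3 | 22.1 | 157 |
| Revised plan, 480/750 | 0.64 | 65.3 | 21.8 | 160 |
| If enrolled means consented: 0.75 × 0.65 | 0.4875 | 49.7 | 16.6 | 210 |

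The last row is there because protocol section 12.1 defines the enrolled population as everyone who signed consent, and SAP 10 reports that about 25% had injury at the screening exam.

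At 65% the binomial standard deviation is √(102 × 0.65 × 0.35) = 4.8, so the 95% range is about 57 to 76 randomised. If the 20% loss that SAP 5 assumes for the primary endpoint also applied to the final platelet test (an assumption), 66.3 × 0.8 = 53.0, or about 18 per group, would have it.

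**3. DAPT duration**

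All patients take open-label DAPT from the index PCI to the 6-month visit. The window is ±2 weeks in SAP 3.3 and ±7 days in SAP Table 2, and an interruption of 5 days or more bars randomisation. With 6 months taken as 182.6 days and a month as 30.44 days:
- ±14 days: 168.6 to 196.6 days, or 5.5 to 6.5 months.
- ±7 days: 175.6 to 189.6 days, or 5.8 to 6.2 months.

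Counted from the index PCI, a cut at 6 months therefore mainly separates early from late attenders.

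**4. Main design**

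For 47% versus 30%, 2:1 allocation, two-sided 0.05 and 90% power, the standard two-proportion formula gives 381 in total against the stated 384. Power at 128 and 256 is 90.3%. Nothing above touches this.

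**The case against.** On the substudy, the best defence is that enrolled was meant as randomised. Groups exist only after randomisation; the footnote to Table 2 says 34 per group without the word enrolled; protocol section 5.3 brings the substudy in just after its post-randomisation testing; 102 is 17 blocks of 6; and the documents use enrolled in more than one sense. This is a fair reading, but it does not rescue the text. Testing starts at screening, so ending with 102 randomised needs a larger tested pool, and no passage plans one. It is also fair that the 65% is trial-wide and the lead site's own yield is not given. Any yield below 100% still falls short of 34.

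On DAPT duration, no criterion bars DAPT before the index PCI (exclusion 3 bars only stenting in the prior year), and the SAP lists pre-admission antiplatelet therapy among its tables. If that exposure counts, the longer stratum could be a real exposure group. This objection stands: the fault is a missing start date, not a proven useless variable.

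On impact, the substudy has no stated hypothesis, power or analysis model. Standard errors would be about √(34/22) = 1.24 times those at 34 per group, but that weakens no inference the SAP claims.

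For the prior-bleeding split I see no benign reading.

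**Conclusion.** Two items are wrong as written.

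- **Prior bleeding.** The recent stratum has an expected count of 0, apart from eligibility violations. Patients with no history are unclassified, and the interaction test cannot be estimated. This rests only on exclusion 7 being applied.
- **Platelet substudy.** The stated 34 per group is not what 102 enrolled patients deliver: about 22 at the SAP's 65% yield and about 31 at the 10% loss first planned. The 22 assumes that enrolled means having passed the screening exam and that the lead site behaves like the trial as a whole.

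The DAPT-duration subgroup is secondary: undefined as it stands, and largely a sort of visit timing if counted from the index PCI.

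A reader might infer that several planned groups cannot be filled. The documents show this for one stratum only. Both DAPT-duration strata can hold patients, and so can all three substudy groups, in smaller numbers. Nor do the documents support reading any of this as a threat to the primary analysis or the main sample size.

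**What to change.** 1. In SAP sections 7 and 9.6, replace the prior-bleeding split by prior GI bleeding: yes (24 months or more ago) versus none.
2. In SAP 9.9.1, either give the expected per-group size at randomisation (about 22 at a 65% yield), or, if that is what was done, state that 102 counts randomised patients and that more were tested at screening. At yields of 64% to 65%, about 157 to 160 enrolled patients would have to be tested for 34 per group. SAP 3.6.1 gives July 2019 for the last enrolment, so this can now only describe what was done.
3. For DAPT duration, return to the protocol's antiplatelet status at enrolment, or state that exposure before the index PCI counts and from when.

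The cost is SAP wording. The downside is a less favourable stated substudy size.

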## **10 Sample size Re-estimation**

Among the first 200 patients enrolled, ~25% had gastrointestinal injury at baseline by screening AMCE (despite clinically absent bleeding or gastrointestinal complaints). Of those who passed the initial exam, only ~65% were eligible for randomization; 17% of patients were noncompliant with the 6-month repeat AMCE exam, and new gastrointestinal ulceration or bleeding was found on the 6-month AMCE examination in 18% of patients. The study sample size was adjusted accordingly so 1000 patients will be screened by AMCE at baseline, with 750 patients enrolled and followed to the 6-month randomization eligibility period to achieve the 480 patients randomized goal.

## **11 Table Listings**

### **1. Enrolled Cohort**

#### **1.1 Registration (Inclusion and Exclusion criteria)**

##### **1.1.1 Baseline demographics (age, sex, height, weight, et al.)**

##### **1.1.2 Baseline clinical and medical history (risk factors, pre-admission antiplatelet therapy, et al)**

##### **1.1.3 Baseline diagnoses**

##### **1.1.4 Baseline laboratory assessment**

##### **1.1.5 Baseline medications**

1.1.6 Baseline procedure details

1.1.7 Discharge medications

1.1.8 Adverse events during baseline hospitalization (cardiovascular, gastric or intestinal, et al.)

1.1.9 Gastrointestinal mucosal injury scoring (MLS and a 5-point scoring system)

1.1.10 AMCE examination details

1.1.10.1 Binary frequency of gastrointestinal mucosal injury at baseline

1.1.10.2 Binary frequency of gastrointestinal mucosal injury at 6 months

1.1.10.3 Binary frequency of clinically evident gastrointestinal hemorrhage attributed to the upper gastrointestinal tract baseline

1.1.10.4 Binary frequency of clinically evident gastrointestinal hemorrhage attributed to the upper gastrointestinal tract at 6 months

1.1.11 Gastrointestinal symptoms assessment (pain, nausea/vomiting, dysphagia, et al)

1.1.11.1 Ordinal frequency of gastrointestinal symptoms assessment at baseline

1.1.11.2 Ordinal frequency of gastrointestinal symptoms assessment at 6 months

1.2.1 Site reported AEs/SAEs

1.2.2 Adjudicated AEs/SAEs

1.2.3 Mortality assessment

1.2.4 Medications adherence (DAPT, PPI, et al)

1.2.4 Subject disposition (lost or consent withdrawn)

1.2.5 Eligibility for randomization evaluation

1.2.5.1 Reasons for randomization ineligibility

## **2. Randomized ITT Cohort**

### 2.1 Registration (Inclusion and Exclusion criteria)

#### 2.1.1 Baseline demographics (age, sex, height, weight, et al.)

#### 2.1.2 Baseline clinical and medical history (risk factors, pre-admission antiplatelet therapy, et al)

#### 2.1.3 Baseline diagnoses

#### 2.1.4 Baseline laboratory assessment

#### 2.1.5 Baseline medications

#### 2.1.6 Baseline procedure details

#### 2.1.7 Discharge medications

#### 2.1.8 Adverse events (cardiovascular, gastric or intestinal, et al.)

#### 2.1.9 Gastrointestinal mucosal injury scoring (MLS and a 5-point scoring system at baseline, 6 months, and 12 months)

#### 2.1.10 AMCE examination details (baseline, 6 months, and 12 months)

##### 2.1.10.1 Binary frequency of gastrointestinal mucosal injury at 12 months

##### 2.1.10.2 Binary frequency of clinically evident gastrointestinal hemorrhage attributed to the upper gastrointestinal tract at 12 months

#### 2.1.11 Gastrointestinal symptoms assessment (pain, nausea/vomiting, dysphagia, et al)

##### 2.1.11.1 Ordinal frequency of gastrointestinal symptoms assessment at baseline

##### 2.1.11.2 Ordinal frequency of gastrointestinal symptoms assessment at 6 months

##### 2.1.11.3 Ordinal frequency of gastrointestinal symptoms assessment at 12 months

### 2.2.1 Site reported AEs/SAEs

2.2.1.1 12 months binary frequency and KM estimates of TLF

2.2.1.2 12 months binary frequency and KM estimates of all bleeding

2.2.1.3 12 months binary frequency and KM estimates of NACE

2.2.1.4 12 months binary frequency and KM estimates of stent thrombosis

2.2.2 Adjudicated AEs/SAEs

2.2.2.1 12 months binary frequency and KM estimates of TLF

2.2.2.2 12 months binary frequency and KM estimates of all bleeding

2.2.2.3 12 months binary frequency and KM estimates of NACE

2.2.2.4 12 months binary frequency and KM estimates of stent thrombosis

